## Abstract

**Background:**

The number of patients with type 2 diabetes is drastically increasing worldwide. It is a serious health problem in Japan as well. Lifestyle interventions can reduce progression from impaired glucose tolerance to type 2 diabetes, and glycemic control has been shown to improve postprandial plasma glucose levels. Moreover, several studies have suggested that continuous interventions (combined diet and exercise) can improve the plasma glucose level and reduce dosage of hypoglycemic agents.

Although many interventional studies of lifestyle education for persons with diabetes in hospitals have been reported, only a few have been clinic-based studies employing an evidence-based lifestyle education program. This article describes the design of a cluster randomized controlled trial of the effectiveness of lifestyle education for patients with type 2 diabetes in clinics by registered dietitians.

**Methods/Design:**

In Japan, general practitioners generally have their own medical clinics to provide medical care for outpatients in the community, including those with type 2 diabetes. With the collaboration of such general practitioners, the study patients were enrolled in the present study. Twenty general practitioners were randomly allocated to each provide patients for entry into either an intervention group (10) or a control group (10). In total, 200 participants will be included in the study. The intervention group will receive intensive education on lifestyle improvement related to type 2 diabetes by registered dietitians in clinics. Lifestyle education will be conducted several times during the study period. The control group will receive information on dietary intake and standard advice on glycemic control by registered dietitians. The primary endpoint is the change from the baseline value of HbA1c at 6 months. Data on health behavior and related issues will be gathered continuously over a 6-month period.

**Discussion:**

This is the first study to evaluate lifestyle education in clinics by a cluster randomization trial in Japan. The proposed study will provide practical information about the usefulness of the intensive lifestyle improvement education program in primary care settings. The study was started in September 2007 and entry of subjects was completed in December 2010. Data on the effect evaluation will be available in 2011.

**Trial Registration:**

UMIN000004049

## Background

The number of patients with type 2 diabetes (T2D) is rapidly increasing, making T2D a serious health problem worldwide. The number of diabetic patients in Japan is increasing as a result of changes in lifestyle and the social environment. Approximately 8.9 million people are estimated to have diabetes based on a hemoglobin A1c (HbA1c) value of 6.1% or more or being recipients of treatment for T2D. Approximately 13.2 million people are at high risk for diabetes, such as those with HbA1c values of 5.6% or more but not greater than 6.1%. Thus approximately 22.1 million people have diabetes or are at high risk for diabetes [1].

Meta-analyses of RCT have shown that lifestyle interventions reduced progression from impaired glucose tolerance to T2D and that glycemic control improved postprandial plasma glucose levels after meals [2-4]. Moreover, in recent years, results of several studies suggest that continuous interventions (combined diet and exercise) can improve the plasma glucose level [5-10] and reduce dosage of hypoglycemic agents [11].

In Japan, lifestyle education for diabetes is mainly conducted in hospitals. However, providing education in outpatient clinics should be effective in increasing participation in lifestyle education by patients with diabetes. In that setting, practical dietary education would be given by registered dietitians. Therefore, to develop evidence-based lifestyle education programs by registered dietitians is important. Furthermore, to conduct effective dietary education, an assessment of nutritional intake is important. A food frequency questionnaire (FFQ) is a feasible method for this purpose. We have developed a FFQ consisting of a list of 82 foods (FFQW82) [12] for use in epidemiological studies. An advantage of the FFQW82 is that patients become aware of their own problems related to dietary habits using this instrument. It may help them to understand the specific relationship between their dietary habits and problems with glycemic control. Recently we developed an intensive lifestyle improvement education (ILIE) program to be conducted by registered dietitians in a community-based clinical setting for patients with T2D.

The aim of this study is to determine the effect of lifestyle education using the ILIE program by registered dietitians for T2D patients in clinics. Effectiveness will be determined by improvements in HbA1c values and other outcome measures.

## Methods/Design

### Study Design

In Japan, many general practitioners (GPs) have their own medical clinics (primary health centers) in which they provide outpatient medical care in the community. Many patients with T2D receive medical treatment by GPs in these clinics. With the collaboration of GPs, study patients were enrolled in the present study.

The study is a cluster randomized controlled trial with two intervention arms. Each unit of the cluster is comprised of 10 patients sent by a collaborating GP. The cluster design is necessary because an individual randomized controlled study has the disadvantage in that when an individual patient is offered an intervention in the same clinic where a different intervention is offered, discussions of details of the intervention among these patients would result in an intra-correlation. The study period will be 6 months. Figure 1 is a flow diagram of the study design.

**Figure 1 F1:**
[figure not shown]
**Study design**. The file contains an overview of the study design.

The primary endpoint is a change from the baseline value of HbA1c at 6 months. Clinical data including that on the patients' HbA1c value will be obtained from the patient's GP. Lifestyle education by face-to-face and/or telephone sessions will be conducted several times during the study period by a registered dietitian. Data on health behavior and related issues will be gathered continuously by the registered dietitian in charge over a 6-month period beginning at entry. Specifically, behavioral changes will be monitored using an assessment sheet and semi-structured interviews. The study was approved by the Medical Ethical Committee of the National Institute of Public Health in Japan in 2006 (NO.NIPH-IBRA#06005).

### Participants and recruitment

Each GP recruited 10 patients who satisfied the criteria for eligibility to participate in the study. When the participating patient gave written informed consent to his/her GP and completed the FFQW82, the informed consent document and FFQW82 were sent to the registered center by the GP and the recruitment was finished.

Study subjects are males and females from 20 to 79 years of age who have HbA1c concentrations of 6.1% or over and are receiving treatment by GPs. For subjects who take oral hypoglycemic medications or insulin, change from the baseline HbA1c level should be less than 0.5% in the previous 3 months. We excluded patients who had proliferative retinopathy over stage 3, were pregnant, had nephropathy or who had difficulty in completing written forms.

In total, a sample size of 200 subjects at high risk for or who have T2D will be recruited (see Figure 1).

### Blinding

Registered dietitians and GPs cannot be blinded to the intervention. Patients will hardly notice which intervention is assigned when he/she is informed of the education process, because only one of the two interventions is given in a specific clinic and the patient cannot be aware of what is going on at another clinic.

### Randomization

Cluster randomization was applied to avoid contamination bias [13]. Clinics are located in the metropolitan area in Kanagawa prefecture, Japan. In 2007 we recruited 24 GPs who expressed interest in participating. We provided details of the study and the standardized intervention that would be provided. We randomly assigned in turn the GP who enrolled the first high risk patient as a participant of this study to either the intervention setting or usual care setting with the use of a randomization list (random permutated blocks with block size 2) during September 2007 to December 2010. In this way, the first 20 GPs were sequentially enrolled to the study. For each GP, 10 patients were enrolled as study participants.

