There are some limitations in this study design. Firstly, the success of this program is to some degree dependent on the dietitian's skill. To address this issue, we have developed a training process for the registered dietitians before the start of the randomization study. Educations in implementing the program are therefore important. Furthermore, the assessment sheet with items ranked according to priority helps standardization of advice by registered dietitians. Secondly, only patients were blinded to the groups. In order to avoid selection bias, we asked GPs to recruit all the patients in turn. Furthermore, we used HbA1c as the primary outcome, which is an objective measure. Although we cannot deny the possibility of the bias, it may be small.

The study began in September 2007 and the enrollment of patients will be completed in December 2010. The 6-month followed up period for all patients will end in June 2011. If this study appears to have positive effects, the behavioral intervention of T2D might also be implemented by other GPs in Japan.

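### Up to 180 of 200 patients may be recruited by a GP who already knows the clinic's arm, and the stated safeguards do not support the claim that any bias may be small

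*Protocol article*

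**What the plan says.** All references are to the protocol article.

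- **Randomization.** Allocation of a clinic follows its first enrolment: "We randomly assigned in turn the GP who enrolled the first high risk patient as a participant of this study". It is made "with the use of a randomization list (random permutated blocks with block size 2) during September 2007 to December 2010". The section continues: "In this way, the first 20 GPs were sequentially enrolled to the study", and "For each GP, 10 patients were enrolled as study participants".
- **Participants and recruitment.** The GP does the recruiting: "Each GP recruited 10 patients who satisfied the criteria for eligibility to participate in the study". The GP also receives the written consent and forwards it to the registration centre. Patients on oral agents or insulin must have had an HbA1c change below 0.5% over the previous 3 months.
- **Blinding.** "Registered dietitians and GPs cannot be blinded to the intervention".
- **Intervention group and Control group.** The dietitian's first session follows within 2 weeks of a patient's entry.
- **Statistical analysis.** A Student's t-test comes first. Linear mixed models are then added: crude (Model 1), baseline-adjusted (Model 2) and multivariate-adjusted (Model 3). None is named primary.
- **Discussion, limitations.** "In order to avoid selection bias, we asked GPs to recruit all the patients in turn". The text adds that HbA1c is objective and concludes: "Although we cannot deny the possibility of the bias, it may be small".

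**The concern.** Randomising clinics balances the clinics. It does not balance the patients within them if those patients are chosen after the arm is known. Here the person who chooses is the GP, who is unblinded and whose clinic may already be running its assigned programme.

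A GP in the intensive arm could, without any bad intent, approach the patients thought most likely to take up a behavioural programme, or those with the most room to improve. A GP in the control arm has no such reason. The arms would then differ in expected 6-month HbA1c change even if the programme did nothing, and the trial would read that difference as an effect.

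The Discussion recognises selection bias, so the question is whether its answer works. Recruiting consecutively is a request made to an unblinded recruiter. Objectivity of HbA1c concerns how the outcome is measured. Patient blinding, also cited there, does not affect the GP's choice of whom to approach. None of this supports a statement about the size of the bias.

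**Working it through.** **1. The plan's own count.** Randomization and Sample size give 20 GPs with 10 patients each: 20 x 10 = 200, as stated.

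**2. Patients open to selection after allocation.** One patient per GP precedes allocation and nine follow: 20 x (10 - 1) = 180, and 180/200 = 90%. This assumes the GP learns the arm at or soon after allocation. Unblinded GPs and a first session within 2 weeks of entry make that plausible, but the article does not state it. If all ten patients per clinic had been listed before allocation was disclosed, the count would be 0.

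**3. Inputs for an illustration of size.** From Sample size: SD 2.2, intra-class correlation 0.1, 10 patients per cluster, 100 per arm.

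- The article does not define the unit of the SD. I read it as HbA1c points.
- That reading fits the stated total only if the 15% effect is taken of an assumed baseline near 8%. With a baseline of 8.05 the difference is 0.15 x 8.05 = 1.21 points. The usual two-mean formula times the design effect gives 99.0 per arm, rounded up to 100, or 200 in total. A baseline of 7.0 gives 262 and 9.0 gives 160.
- Taking 15 and 2.2 on one scale gives 1 patient per arm before the design effect, so that cannot be the basis.

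**4. Standard error.**

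- Design effect = 1 + (10 - 1) x 0.1 = 1.9
- SE of the difference = 2.2 x sqrt(2 x 1.9/100) = 0.429 points

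**5. Effect of an assumed shift.** Let the nine exposed patients per clinic differ between arms by s points in expected 6-month change, with no true treatment effect. The arm means then differ by 0.9 x s. The non-centrality is 0.9 x s/0.429, referred to a t distribution with 20 - 2 = 18 degrees of freedom, two-sided 5%, without baseline adjustment.

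| Assumed shift s (points) | s as a fraction of SD | Bias 0.9 x s | Non-centrality | Rejection of a true null |
|---|---|---|---|---|
| 0.22 | 0.1 | 0.198 | 0.46 | 7.2% |
| 0.44 | 0.2 | 0.396 | 0.92 | 14.1% |
| 0.66 | 0.3 | 0.594 | 1.39 | 25.9% |

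The shifts are assumptions, since the article gives nothing from which to estimate them. The calculation is also on untransformed HbA1c, whereas the plan analyses log-transformed outcomes.

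**6. What the plan already limits.** The stability criterion makes it harder to enrol a medicated patient at a transient peak. It does not cover unmedicated patients. Models 2 and 3 adjust for measured baseline differences. Neither measure reaches an unmeasured characteristic such as motivation.

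**The case against.** The strongest reply is that the protocol is open about the limitation and has done more than nothing. GPs were asked to take all patients consecutively, which would remove the problem if it were followed. The stability criterion and the adjusted models deal with much of the selection on glycaemic level, and the error rates above ignore that adjustment. Screening logs, and the time at which each GP was told the arm, are details an article may leave to the full protocol. All of this stands. It limits the size of the point but does not remove it: the article sets out the recruitment sequence and then defends it with an argument about measurement and an unsupported statement of size.

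A reader might infer more than the text supports:

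- **That 180 patients were in fact chosen with the arm known.** The article does not say when each GP learned the arm, so 180 is a bound.
- **That each clinic recruited for three years.** September 2007 to December 2010 is the window for the whole trial. No time per clinic is given.
- **That blocks of 2 push the count to 190 (10 x 9 + 10 x 10).** This needs the second GP in each block to know both the block size and the previous assignment, which nothing in the article suggests.
- **That the assumed shift applies to the whole arm.** The rates would then be 7.7%, 16.3% and 30.8%, but the first patient in each clinic precedes allocation.
- **That regression to the mean is left unchecked.** The stability criterion and baseline adjustment both act against it.

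**Conclusion.** The concern holds as a weakness of design and of the stated defence. Up to 180 of 200 patients (90%) may have been selected by a GP who knew the arm. The only safeguard aimed at recruitment is a request, and the conclusion that the bias may be small has no data behind it. Selection on glycaemic level is partly contained by the eligibility criterion and the planned adjusted models. Selection on unmeasured factors is not.

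That the sequence leaves this opening follows directly from the text. How much bias resulted, if any, cannot be known from the article. The error rates of about 7%, 14% and 26% are illustrations. They rest on assumed shifts, SD 2.2 read as HbA1c points, intra-class correlation 0.1, 18 degrees of freedom and no baseline adjustment. They show that a modest shift would matter with 10 clinics per arm, not that one occurred. The documents do not support a charge of concealment, since the limitation is disclosed.

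**What to change.** **Analysis.** Name the baseline-adjusted linear mixed model (Model 2) as the primary analysis, in place of the unadjusted t-test. It is already planned, so the change costs nothing beyond fixing its status. It reduces bias from selection on baseline HbA1c.

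**Reporting.**

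- Give baseline characteristics by arm.
- Give the numbers eligible, approached and refused by arm, as far as clinic records allow.
- Compare each clinic's first patient with its later patients by arm. With only 10 first patients per arm this is descriptive.
- Replace the statement that the bias may be small with these data, and say that residual selection on unmeasured factors cannot be excluded.

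**Any clinic not yet allocated.** Release the allocation only after the GP has sent the registration centre an ordered list of eligible patients, and enrol in that order. This may no longer be possible: the Abstract says entry was completed in December 2010, while the Discussion still puts completion in the future.

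**Cost.** A short delay for any such clinic and a little more analysis and reporting. No additional patients are needed.

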### Intervention and control groups

#### Intervention group

A registered dietitian in charge will make the first contact with the patient within 2 weeks from entry and hold the first session. Subjects in the intervention group will have 3 or 4 individual sessions by the registered dietitian in the 6-month period, with the second session held within a month after the first session. Also, 3 months after the first session, the participant will receive the subsequent individual session. Between the second session and the 6th month, the dietitian will contact the patient by telephone or provide a face-to-face counseling session 2-3 times to reinforce the dietary or physical activity advice and give additional support. (see Figure 1) The intensive lifestyle improvement education (ILIE) program consists of 4 strategies for glycemic control (Table 1). We developed the ILIE program based on some of the strategies described in previous studies [14-16]. Specifically, nutritional education will provide scientific information on glycemic control. Examples of advice given are to reduce energy intake at dinner and to eat one or two portions of fish/lean/meat or poultry/egg/soybean products and two portions of vegetables at each meal. A characteristic of the ILIE program is that registered dietitians can identify for patients problems of lifestyle which most often affect glycemic control by using an assessment sheet that describes matters that should be given priority for glycemic control. We made the assessment sheet by consulting evidence-based practice guidelines for treatment of diabetes in Japan [17]. Five registered dietitians decided on the priority items on the assessment sheet based on empirical evidence, with items on the upper half being more important than those on the lower half. This will help dietitians to make an objective appraisal of what practical advice to give to patients. Patients will decide on one or two short-term goals for glycemic control to be achieved in the subsequent 1 or 3 months based on the results of the FFQW82 and advice by a registered dietitian. On the other hand, for overweight or obese patients, the subject will be recommended to achieve a modest (at least 3%) weight loss. Sedentary participants will be encouraged to increase basal physical activity. We will recommend a gradual increase in physical activity in daily life rather than a formal fitness regimen or sports activity during leisure time. Several telephone follow-up calls will be made to assess progress toward the short-term goal and to offer solutions to barriers against achieving that goal. At that time, subsequent short-term goals will be decided upon.

**Table 1 T1:** Content of Lifestyle Education Program for T2D

Content of Education	Topics
Basic information on glycemic control	Target values for body weight, HbA1c, blood pressure, blood lipids
	Diabetes complications
	Mechanism of changing of plasma glucose levels
	Effect of exercise on plasma glucose
	Needed energy intake for 1 day
	Dietary composition
Actions for glycemic control	Setting goals for glycemic control
	Solving barriers to achieving goals
Daily activities for glycemic control	Frequency and quantity of effective activity
	Setting goals for daily activity
Managing stress for glycemic control	Ways of coping with stress

##### Training of health professionals

In the 3-month period before the start of the intervention, registered dietitians received relevant training sessions with regard to the intervention protocol. Several meetings about the aspects and basic principles of the intervention protocol took place (i.e. the screening procedure, self-management principles, client centeredness, motivational interviewing, interdisciplinary collaboration, assessment tools, parts of the toolbox and referrals). Before the start of the study, registered dietitians had the opportunity to gain experience with the intervention protocol under supervision by the project team.

##### Control group

A registered dietitian in charge will make the first contact with the patient within 2 weeks from entry into the study and hold a first session. Patients in the control group will receive information on dietary intake estimated using the FFQW82 and standard advice on glycemic control by registered dietitians. They will receive the usual care provided in the outpatient clinic and can use or apply for all services previously available to them.

### Study hypothesis

The hypothesis underlying the study is that participation in the intensive dietary education group would decrease the HbA1c value by 15% from baseline (primary endpoint) in the intervention group after 6 months of education whereas such a decrease would not occur in the control group. We assumed that the HbA1c value of the control group would not change. The value of 15% increase in the HbA1c value was decided through reference to a study conducted in the USA [14] and through our experience with a previous survey [18].

### Outcome measures

The primary outcome measure is a decrease from the baseline HbA1c level after 6 months of education. The difference in the primary endpoint between intervention and control groups is the effect size of the present study. Secondary outcome measures are the differences from baseline for body mass index (BMI), waist circumference, blood pressure, fasting plasma glucose lipid profile, and the difference in energy and nutrition intakes (whole day and each meal) assessed using the FFQW82. Measurements will be made at baseline and at 6 months.

